### Interventions

2.4

The interventions in this study will be conducted for 12 weeks. HBT group will receive home-based exercise program consisting of 9 strengthening, walking, task-related and balance exercises, which aim to improve muscle strength, balance and gait ability. The exercises were designed based on a protocol reported in a previous study^[14]^ and using the frequency, intensity, time and type (FITT) principle.^[15]^ The total duration of the exercise program is between 45 to 60 minutes, depending on the participants ability. Participants will be instructed to perform the given exercises at a comfortable pace for 3 times per week, monitored or assisted by their caregivers. Training session will be provided to all participants and caregivers by the main researcher prior to implementing home-based sessions. Logbook will be given to all participants to document their home-based exercise sessions. The graphic and instructions for exercises in the logbook were adopted from an exercise website (https://www.physiotherapyexercises.com/). Once per 2 weeks telephone call will be attempted for each participant to monitor their exercise adherence and occurrence of any potential adverse effects related to exercise such as muscle soreness and cramps. Exercises will be progressed with regards to intensity for participants who report no adverse effects. Table 1 shows the home-based exercise program to be provided to participants in HBT group.

**Table 1 T1:** Home-based exercise program for HBT group.

Warm up exercise (stretching exercise)
• Head turn with over pressure
• Neck lateral flexor stretch
• Posterior shoulder stretch
• Trunk rotation
• Hamstring stretch in sitting
• Seated gluteal stretch
1. Sit to stand exercise – any one exercise from the list below according to participant's standing balance and lower limb muscle strength:
• Sit to stand with support
- participant with poor standing balance
• Sit to stand without support
- participant with fair/good standing balance and muscle strength 3/5
• Sit to stand in tandem position
- participant with good standing balance and muscle strength above 4/5
• Sit to stand on a low stool
- advance participant with good standing balance and muscle strength above 4/5
2. Stepping in different directions
3. Stepping up and down stairs or a block
4. Reach to target exercise – any one exercise from the list below according to participants standing balance:
• Stand and reach to targets
- participant with fair standing balance
• Step and reach to targets
- participant with good standing balance
• Sit and reach to targets
- participant with poor standing balance
5. Walk and pivot turn exercise
6. Sideway walking exercise – either one exercise from below according to participants standing balance
• Cross over side step
- participant with good standing balance
• Walk sideway
- participant with fair/good standing balance
7. Walk with stepping exercise – either one exercise from below according to participants standing balance and lower limb muscle strength
• Walking Lunge
- participant with fair/good standing balance and muscle strength above 3/5
• Walking with big step
- participant with fair standing balance and muscle strength above 3/5
8. Wall push-ups
9. Arm Exercise – any one exercise from the list below according to participants upper limb muscle tone and strength
• Upper limb proprioception exercise
- participant with muscle tone above 1+
• Upper limb active range of exercise
- participant with muscle tone above 1 and muscle strength below 3/5
• Upper limb strengthening exercise
- participant with normal muscle tone and muscle strength 3 and above

HBT = home-based therapy.

Meanwhile participants in UP group will be advised to perform exercises as prescribed by the therapist prior to discharged from physiotherapy service. This is the common practice among the attending therapists when discharging stroke patients. Similarly, participants will be monitored in term of exercise adherence and occurrence of any potential adverse effects related to exercise such as muscle soreness and cramps via telephone call once in every 2 weeks. Participants will also be asked to record their exercise practice in a logbook.

### Outcomes

2.5

Feasibility of both interventions will be assessed with regards to patients acceptance and adherence, and the occurrence of adverse effect.

1.Stroke survivors acceptance will be collected during post-trial assessment with question of “What do you think about this home-based therapy?”. Response from the survivors will be categorized into positive and negative responses and analysed descriptively.2.Adherence rate will be reported in term of percentages of practice (number of sessions performed out of the total sessions required i.e., 36 sessions). Number of practice sessions performed will be obtained from participants logbook.3.Occurrence of adverse effects related to exercise such as muscle soreness, cramps and muscle strain will be monitored through telephone call (once every 2 weeks) and during post-trial assessment.

The intended outcomes of the interventions in this study are:

1.Functional performanceTime up and go (TUG) test will be used to assess mobility level and falls risk. The cutoff point of high risk of fall for stroke survivor is >14 seconds.^[16]^ TUG was shown to have high test-retest reliability (ICC = 0.96) and excellent correlation with the comfortable gait speed test (r = −0.86), fast gait speed test (r = −0.91), ascending stair climbing test (r = 0.86), descending stair climbing test (r = 0.90) and 6-minute walk test (r = 0.92).^[17]^ Participants will be instructed to stand up from a standard chair and walk safely as quickly as possible for 3-meter, turn around and walk back to the chair and sit down. The timing begins at the instruction “Go” and stops when participants sit down on the chair.The 10-meter walk test (10mWT) will be used to assess walking speed among participants and determine the functional ambulatory classification of each participants. The participant will be instructed to walk along the 10-meter walkway and stop at the end point with comfortable speed. The middle of the 6-meter walkway will be timed as the participant walks. The test will be repeated with fast walking speed. The 10mWT has high test-retest reliability (ICC = 0.95–0.99) in stroke survivors.^[18]^2.Self-efficacy: The stroke self-efficacy questionnaire (SSEQ), a 13-item self-administered questionnaire which designed specifically for stroke survivors will be used to assess the level of self-efficacy among the study participants. SSEQ consists of two self-efficacy domains: activity (items 1 to 8) and self-management (items 9 to 13).^[19]^ Participants need to rate their confidence level on a 3-point scale, from 0 which indicates “not at all confident” to 3 which represents “very confident”. The total score of SSEQ will be calculated by summation of each item score. Higher score of SSEQ indicates higher self-efficacy level.^[19]^ SSEQ has good reliability, with Cronbach α coefficient value 0.90 and person separation index (PSI) > 0.80 for both activity and self-management domains.^[19]^3.Anxiety level: Hospital anxiety and depression scale (HADS)^[20]^ will be used to measure anxiety level of the patient. HADS is divided into an anxiety subscale (HADS-A) and a depression subscale (HADS-D), each subscale contains 7 questions and can be calculated separately. HADS-A will be used to assess the anxiety level among participants at baseline and post-trial. The cut-off score for anxiety using HADS-A is 8 and above, with specificity of 0.78 and a sensitivity of 0.9. Bjelland et al^[21]^ who reviewed HADS in 747 studies reported that HADS-A has good reliability value, indicated by Cronbach's α coefficient between 0.68 to 0.93.

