**Methods::**

This is an assessor-blinded randomized control trial comparing 2 types of intervention which are HBT (experimental group) and usual practice (UP) (control group). Based on sample size calculation using GPower, a total number of 42 participants will be recruited and allocated into either the HBT or the UP group. Participants in HBT group will receive a set of structured exercise therapy consisting of progressive strengthening, balance and task-related exercises. While participants in UP group will receive a usual “intervention” practised by rehabilitation professional prior to discharging stroke patients from their care. Both groups are advised to perform the given interventions for 3 times per week for 12 weeks under the supervision of their caregiver. Outcomes of interventions will be measured using timed up and go test (for mobility), ten-meter walk test (for gait speed), stroke self-efficacy questionnaire (for self-efficacy) and hospital anxiety and depression scale (for anxiety level). All data will be analyzed using descriptive and inferential statistics.

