### Study participants

2.2

Potential participants will be recruited by the main researcher; inclusion criteria are as follows:

1.Clinically diagnosed as stroke by a medical officer.2.Completed hospital-based rehabilitation and scheduled for discharge.3.Age 18 to 80 years old. (to minimise risk of frailty which is prevalent in those above 80)^[13]^4.Availability of carer to monitor home-based interventions.5.Score 3 or more on functional ambulation categories (FAC) (3: ambulator-dependent for supervision; 4: ambulator-independent level surface only; 5: ambulator-independent)

Exclusion criteria are:

1.Score below 20 on Montreal Cognitive Assessment (MoCA) which indicates presence of cognitive impairment.2.Score 4 or more on a Modified Rankin Scale (4: moderate severe disability; 5: severe disability; 6: death).3.Attended by a home physiotherapist after discharged from HOS.4.Score above 11 on Hospital anxiety and depression scale -depression subscale (HADS-D) which indicates moderate to severe depression.5.Presence of other medical conditions such as severe neurological and musculoskeletal disorders or comorbidities.

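### Adverse-effect recording is limited to exercise-related effects and does not name falls, so falls between sessions lie outside it in both arms

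*Protocol article*

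**What the plan says.** Section 2.5 makes adverse effects one of three feasibility components, for both arms: "Feasibility of both interventions will be assessed with regards to patients acceptance and adherence, and the occurrence of adverse effect". It then sets the scope: "Occurrence of adverse effects related to exercise such as muscle soreness, cramps and muscle strain will be monitored through telephone call". The calls are two-weekly, and the item is also covered at the post-trial assessment.

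Section 2.4 gives the home-based therapy (HBT) and usual practice (UP) arms the same monitoring. For UP it reads: "occurrence of any potential adverse effects related to exercise such as muscle soreness and cramps via telephone call once in every 2 weeks". In the HBT arm the same report has a further use: "Exercises will be progressed with regards to intensity for participants who report no adverse effects".

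Falls appear elsewhere, but not as a recorded event. The abstract and the Discussion list them among the consequences of decline after discharge. Section 2.5 uses the timed up and go (TUG) test to gauge falls risk. Section 2.2 admits participants from functional ambulation category 3 upwards ("3: ambulator-dependent for supervision"). Table 1 prescribes multi-directional stepping, stair or block stepping and pivot turning without tying them to a balance grade, and elsewhere provides options for participants with poor standing balance.

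Sessions take place with a carer. The abstract says: "Both groups are advised to perform the given interventions for 3 times per week for 12 weeks under the supervision of their caregiver". Section 2.4 describes HBT sessions as "3 times per week, monitored or assisted by their caregivers".

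**The concern.** Each of the three statements of the adverse-effect item carries the same limit, relatedness to exercise, and each illustrates it with muscle complaints alone. A participant or caller following that wording has no prompt to mention a fall, and has a reason to leave out one that happened away from a session.

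Two things are at stake. First, the adverse-effect component of feasibility could look favourable because falls were under-recorded. Second, HBT could plausibly raise falls (harder balance tasks) or lower them (better mobility). Neither direction can be described by arm if some falls are filtered out at collection on a judgement of relatedness. The article does not say who makes the calls or that judgement; the only blinding it states is that of the outcome assessor. Events not asked about at the time cannot be recovered at analysis.

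**Working it through.** The plan states no figure on this point, so there is none to reproduce. The check is a reading of the text, followed by a sizing under stated assumptions.

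**Step 1: what the wording covers.**

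| Event | Within the adverse-effect wording? |
|---|---|
| Muscle soreness, cramp or strain from exercise | Yes, named |
| Fall during an exercise session | Yes, by the open wording, but not named |
| Fall between sessions | No, unless linked to exercise |
| Fall in either setting not judged exercise-related | No |

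The examples are illustrative, so they do not close the list. The relatedness limit is separate and stays whatever is added to the examples.

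**Step 2: does another item fill the gap?** The TUG is a timed test at baseline and week 12. It estimates risk and does not count falls. The logbook is described as a record of exercise practice. Nothing else in the article records falls.

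**Step 3: size.** Inputs: 21 per arm (section 2.7). The 12-week risk of falling, p, is an assumption because the article gives none; it is varied from 5% to 40%.

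- Expected participants who fall, per arm: 21 × p.
- Chance of at least one in an arm: 1 − (1 − p)^21.
- Power to detect a doubling (two-sided 0.05, normal approximation), with q = 2p and m = (p + q)/2: Φ{[(q − p) − 1.96 √(2m(1 − m)/21)] / √([p(1 − p) + q(1 − q)]/21)}.
- Worked case, p = 20% against 40%: [0.20 − 1.96 × √(2 × 0.3 × 0.7/21)] / √((0.16 + 0.24)/21) = (0.20 − 0.277)/0.138 = −0.56, so power is about 29%.

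| Assumed p | Expected fallers of 21 | Chance of at least one | Power to detect a doubling |
|---|---|---|---|
| 5% | 1.05 | 66% | 9% |
| 10% | 2.1 | 89% | 14% |
| 20% | 4.2 | 99% | 29% |
| 30% | 6.3 | over 99% | 50% |
| 40% | 8.4 | over 99% | 77% |

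- Upper one-sided 95% bound after no fallers in 21: 1 − 0.05^(1/21) = 13.3%.

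These are counts of participants who fall, not of falls. They are not counts of missed events either. Some falls would occur in sessions and fit the present wording, and the article gives no basis for the split.

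**The case against.** The strongest reply is that this is a condensed article. The call script, logbook layout and post-trial form are not shown, and question wording is commonly left to the full protocol. The text is open-ended, so a fall while stepping or turning in a session is already in scope. The arms are monitored on the same schedule and in the same terms, so no differential recording is written in. With 21 per arm a real difference in falls would probably be missed even if every fall were captured: power for a doubling is 14% from 10% and 29% from 20%.

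Most of that stands, and it rules out several stronger readings that a reader might infer:

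- That monitoring covers muscle complaints only. They are examples, not a closed list.
- That participants are never asked about falls. The questions are not shown, so this cannot be established.
- That the exercise is unsupervised. A carer is an entry requirement and oversees sessions, although no professional is described as present.
- That HBT will be declared safe on the strength of soreness reports. No safety conclusion is planned; adverse effects are one part of feasibility.
- That falls are the trial's rationale or its main foreseeable harm. The article lists them among several consequences of decline. Table 1 also reserves lunges for participants with adequate balance and strength, although stair stepping and pivot turning carry no such condition.

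One thing is not answered. The article does not merely leave detail out; it states a scope. A fuller document consistent with that scope would still exclude falls not related to exercise.

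**Conclusion.** The point holds as a minor one. Followed literally, the adverse-effect item takes in falls during sessions without naming them and leaves out falls between sessions or not judged exercise-related, in both arms alike. The feasibility component could therefore under-record falls and could not describe all of them by arm. This rests on the article's stated scope and on the absence of any other item that counts falls; a full protocol that records all falls would settle it.

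The size is uncertain. At an assumed 10% to 30%, about 2 to 6 participants per arm would fall in 12 weeks, and an unknown share of those falls would lie outside the wording. Complete capture would add descriptive information, not a test of a difference. The effectiveness outcomes and their analysis are not affected.

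**What to change.** In sections 2.4 and 2.5, name falls as a recorded event. At each existing two-weekly call and at the week-12 assessment, ask in identical words in both arms:

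- whether there has been any fall since the last contact;
- whether it happened during exercise;
- whether it led to injury or a medical visit.

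Dating the question from the last contact also covers a missed call, which matters because the HBT calls are described as attempted. Record every fall whatever its judged relatedness, and report participants who fell and numbers of falls descriptively by arm, beside the other adverse effects.

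The cost is slightly longer calls, an added line in the adverse-effect table and a minor amendment. No new visit or test is needed. No change to the exercise progression rule is proposed.

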
### Assessment of outcomes

2.6

All participants will be assessed at baseline and at the end of week 12 of interventions by a therapist who is blinded to the group allocation and trained to conduct the standardized tests. To avoid recall bias, the recorded baseline assessment data will not be accessible to the blinded assessor during the post-trial assessment.

### Sample size

2.7

GPower software version 3.0.10 was used to estimate required sample size for this study. This study used mixed model analysis of variance (ANOVA) to analyze time, group and interaction effects of the interventions. Therefore F-test (ANOVA repeated measure, within-between interactions) were chosen. The study power was set at 80% and alpha value set at 0.05. Based on these, a minimum sample of 42 subjects is required, i.e., 21 participants in each arm.

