### Data analysis

2.8

All data will be entered into IBM Statistical Packages for Social Sciences (SPSS) version 23.0. Intention-to-treat (ITT) method will be used; all the participants recruited at baseline will be included in the outcome analysis. Using ITT, missing data will be replaced with last observation carried forward. Socio-demography and health profile of the participants will be analyzed descriptively and reported as frequencies (percentages) and mean (standard deviation) or median (inter-quartile range). The effects of the interventions will be analyzed using mixed model ANOVA and reported as main time, group and time-group interaction effects for each intervention outcome. Level of significance will be set as *P* < .05 for all results.

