### Ethics and dissemination

2.9

This study received ethical approval from the Research and Ethics Committee of Universiti Kebangsaan Malaysia and the National Medical Ethics and Research Committee (NMERC) (study ID: NMR–19–941–46993). NMERC, being an independent research committee under the Malaysia Ministry of Health is also responsible in monitoring the study progress. All participants will be asked to provide an informed consent prior to participating in the study by the main researcher. Participants can withdraw anytime during the study without providing an explanation. Participants personal information and data will be kept confidential. Investigators in this study will have access to the final trial dataset. The findings of this study will only be published in a peer-reviewed journal.

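### The 42 participants called the minimum for 80% power are also the whole recruitment total, so no dropout margin is visible under a last-observation-carried-forward rule that scores each dropout as no change

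*Protocol article*

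**What the plan says.** Four parts of the protocol article bear on this.

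- **Sample size (2.7)** names the test: "Therefore F-test (ANOVA repeated measure, within-between interactions) were chosen". It gives the error rates: "The study power was set at 80% and alpha value set at 0.05". It then concludes: "Based on these, a minimum sample of 42 subjects is required, i.e., 21 participants in each arm".
- **Abstract, Methods** sets the recruitment target at the same number: "a total number of 42 participants will be recruited and allocated into either the HBT or the UP group".
- **Assessment of outcomes (2.6)** fixes two measurements: "All participants will be assessed at baseline and at the end of week 12 of interventions". **Data analysis (2.8)** includes everyone recruited and adds: "Using ITT, missing data will be replaced with last observation carried forward".
- **Ethics and dissemination (2.9)** foresees loss: "Participants can withdraw anytime during the study without providing an explanation".

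No dropout rate appears anywhere in the article.

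**The concern.** A number described as the minimum for 80% power should be the number analysed with usable data. Here it is also the number recruited. Any loss must then come out of the stated power unless 42 already holds a margin, and the text does not say that it does.

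The missing-data rule does not close the gap. With one post-baseline visit, the last observation for a dropout is the baseline value, so that participant's change is set to zero. The analysed count stays at 42, but when both arms lose participants the between-arm difference is pulled towards zero. A reader who sees 42 analysed and 80% planned would take the power as intact. At stake is how a non-significant result is read when the trial reports whether HBT is better than usual practice.

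**Working it through.** **Inputs from the article.** Alpha 0.05, power 80%, the repeated-measures within-between interaction F-test, two arms of 21, two measurements. **Not given in the article:** effect size, SD, baseline-to-week-12 correlation (ρ) and dropout rate (q).

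**1. Can 42 be reproduced?** For this procedure the noncentrality is λ = 2Nf²/(1−ρ), with 1 and N−2 degrees of freedom. The listed inputs alone do not fix N:

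| f | ρ | N for 80% power |
|---|---|---|
| 0.10 | 0.5 | 200 |
| 0.20 | 0.5 | 52 |
| 0.25 | 0.5 | 34 |
| 0.25 | 0.8 | 16 |

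So 42 can only be worked backwards.

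**2. What 42 implies.** With two arms and two times, the interaction test is a two-sample t-test on change, and λ = Nd²/4, where d is the between-arm difference in change divided by the SD of change. With 1 and 40 degrees of freedom, 80% power needs λ = 8.243. Hence d = √(4 × 8.243/42) = 0.886. At ρ = 0.5 this is f = 0.886/4 = 0.2215. Because N moves in steps of two, any f from 0.2215 to about 0.227 at ρ = 0.5 returns 42.

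**3. Effect of carrying the last observation forward.** Let a proportion q drop out of each arm and be scored as zero change. With the SD of change set to 1, an arm with mean change μ then has mean (1−q)μ and variance (1−q) + q(1−q)μ². Take arm means 0.886 and 0 and q = 0.20:

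- difference = 0.8 × 0.886 = 0.709
- variances = 0.8 + 0.16 × 0.785 = 0.926, and 0.8; pooled SD = √0.863 = 0.929
- effective d = 0.709/0.929 = 0.763; λ = 42 × 0.763²/4 = 6.11; power 67.5%

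The formula and a simulation of 40,000 runs agree to within about one point:

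| Dropout, equal in both arms (assumed) | Power, 42 recruited, d = 0.886 |
|---|---|
| 0% | 80% |
| 5% | about 77% |
| 10% | about 75% (74 to 75) |
| 20% | about 68% |
| 30% | about 61% |

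**4. Completers only, 20% loss.** 42 × 0.8 = 33.6, taken as 34. λ = 34 × 0.785/4 = 6.67 with 32 degrees of freedom gives 70.7% power. The difference detectable with 80% power becomes 0.99 SD of change.

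**5. Week-12 value adjusted for baseline, same 34 completers.** With equal variances at both times, a difference of 0.886 SD of change is 0.886√(2(1−ρ)) outcome SDs, and the residual SD is √(1−ρ²). The ratio is 0.886√(2/(1+ρ)). With 31 degrees of freedom:

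| ρ | Effective d | Power |
|---|---|---|
| 0.5 | 1.023 | 82% |
| 0.7 | 0.961 | 77 to 78% |
| 0.8 | 0.934 | 75% |
| 0.9 | 0.909 | 73% |

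**6. Another possible origin of 42.** f = 0.25 with ρ = 0.5 (d = 1.0) needs 34, and 34/0.8 = 42.5. At d = 1.0, 42 gives 88.5% power with no loss. Under the carry-forward rule it gives 83%, 80% and 77% at 10%, 15% and 20% equal dropout.

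**The case against.** **An article condenses.** The software cannot run without an effect size, so one was entered and not printed. This stands: the missing effect size and correlation are not a finding by themselves. What the article does print is a minimum, a recruitment total equal to it, and a missing-data rule, and these do not fit together without comment.

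**0.89 SD is not the plan's figure.** This also stands. It follows only if 42 is an uninflated minimum. The word minimum favours that reading without proving it. Step 6 shows a rival origin with a margin built in, but then 34 and not 42 would be the minimum, and section 2.7 would still need correcting.

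**A reader might infer that any dropout takes power below 80%, whatever effect was assumed.** The documents do not support that. At 1.0 SD of change, 42 tolerates about 15% equal dropout. The pattern of loss matters too. If usual practice declines by 0.886 SD, HBT holds steady and only HBT loses participants, the carried-forward zero equals the true HBT mean. Simulated power then rises to about 82%, 84% and 86% at 10%, 20% and 30% loss.

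**A reader might also infer that the trial is insensitive to moderate effects.** At N = 42, power is 35% for 0.5 SD and 60% for 0.7 SD of *change*. In SDs of the outcome, the difference detectable with 80% power is 0.886√(2(1−ρ)): 0.89 at ρ = 0.5, 0.56 at 0.8 and 0.40 at 0.9. The article gives no 12-week correlation, so the claim cannot be made in outcome units.

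**Conclusion.** The point holds in limited form. The stated 80% power has no visible margin for loss, and the plan's own missing-data rule does not protect it. If 42 is the uninflated minimum, it corresponds to about 0.89 SD of change with complete data, and power falls to roughly 75% at 10% and 68% at 20% dropout.

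This rests on three assumptions: the 0.89 SD is inferred, dropout is equal in the two arms, and the dropout rates are illustrative. If 42 already contains an allowance, the power may be adequate and the error lies in calling 42 the minimum. Either way section 2.7 needs correcting. The material does not show that the trial is underpowered for its true target, because that target is not stated.

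**What to change.** Keep 42.

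- **Section 2.7.** Name the outcome used for sizing and the effect size and correlation actually entered. Say whether 42 includes dropout. Restate power under the expected loss. If the entered effect was 0.89 SD of change, 34 completers give about 71% power for the planned comparison of change, and a detectable difference of about 0.99 SD of change. The 0.89 should not be adopted as the target merely because it can be worked back from 42.
- **Section 2.8.** Compare week-12 values between arms, adjusted for the baseline value already collected, instead of relying on the time-by-group interaction with carried-forward values. With 34 completers this gives about 82%, 78%, 75% and 73% power at correlations 0.5, 0.7, 0.8 and 0.9, against 71% for unadjusted change. It recovers part of the loss, and most of it only at the lower correlations.

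Cost: a less favourable stated figure and a small change to the analysis text. The adjusted comparison of completers also needs a sentence on how participants without a week-12 value are handled, since section 2.8 now promises to include everyone. No participants or visits are added.
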